**Primary Endpoint Analysis**
The primary endpoint is the reduction in LH pulse frequency during the 4-hour period following Ganirelix administration.
Analysis will include:
- Determination of LH pulse frequency using the method described above (1.1.2).

**Secondary Endpoint Analyses**
- LH variation (mean, basal and total LH) before and after Ganirelix injection will be assessed.
- Androgen production variation will be evaluated as the difference in total testosterone and androstenedione levels between H8 and H0 (4 hours post- vs. pre-injection).
- FSH, estradiol, and AMH concentrations will be compared between H0 and H8 to assess hormonal changes after treatment.

**Handling of Missing Data**
Given the short study duration and intensive monitoring, missing data are expected to be minimal. Any missing measurements will be described, and no imputation is planned. Analyses will be based on available data only.

**Statistical Software**
All statistical analyses will be performed using:
10.0.2 GraphPad Prism software (GraphPad; San Diego, CA, USA)

**Justification for the Absence of a Power Calculation**As this is an **exploratory study** no formal sample size calculation or statistical power analysis has been performed. The main objective of this research is to generate preliminary physiological and pharmacodynamic data on the effect of low-dose Ganirelix on LH pulsatility in women with PCOS, rather than to formally test a hypothesis.
Given the mechanistic and proof-of-concept nature of the study, the selected sample size of 20 participants is deemed appropriate to:
- Evaluate feasibility and study logistics;
- Provide initial estimates of variability in LH pulse frequency and amplitude under low-dose GnRH antagonist treatment;
- Support the design of a future adequately powered confirmatory trial.
This approach is consistent with international regulatory guidance for early-phase exploratory studies (ICH E9, EMA guidelines on exploratory trials), which emphasize estimation over formal hypothesis testing in pilot settings.

## 13 QUALITY CONTROL AND ASSURANCE

**Conduct of the study**

A start-up meeting with the principal investigator will be held before the beginning of the study to review Good Clinical Practice (GCP) requirements, the organization of the trial, and the planned monitoring procedures.
The investigator will inform the sponsor in real time of all inclusions made.

Medical observations will be kept in the patient’s medical record, and all study-related data will be entered into the designated case report forms (CRFs) in accordance with Good Clinical Practice. These forms will document each step of the participant’s management according to the study protocol.
Any protocol deviation will be documented along with its justification.
Data collection must be exhaustive and will be regularly verified by a Clinical Research Associate (CRA), according to the procedures defined in the protocol (if applicable).

**Monitoring of the study**

Monitoring will be conducted according to the monitoring plan approved before the start of the study or triggered by a specific request from the sponsor’s CRA. The frequency and extent of monitoring activities will depend on the number of inclusions and study progress.

During on-site monitoring visits, CRAs must be able to access:

- The patients’ case report forms (CRFs)
- The medical and nursing records of enrolled participants
- The investigator site file

Monitoring will verify at least the following points:

- The existence of participants and the presence of signed informed consent forms
- Compliance with inclusion criteria
- Verification of the primary endpoint
- Recording and reporting of serious adverse events (SAEs)
- Occurrence of any new information requiring the submission of a protocol amendment
- Management and monitoring of investigational product handling by the pharmacy

**Closure of the study**

At the end of the study, closure procedures will be implemented, including the organization and filing of all source documents and data. Once the final analysis has been completed and validated, all study documentation and data will be sealed and archived according to specific procedures in secure facilities.

## 14 ETHICAL AND LEGAL CONSIDERATIONS

The study will be conducted in accordance with the approved protocol, the French Public Health Code, the principles of Good Clinical Practice (GCP) of the European Union, and all applicable regulatory requirements.
The trial will be registered in the public database ClinicalTrials.gov.

### Ethics Committee and Competent Authority

Authorization from the Competent Authority and opinion from the Ethics Committee

Before the beginning of the research, the sponsor will submit an authorization request to the ANSM (Agence Nationale de Sécurité du Médicament et des Produits de Santé) and will obtain a favorable opinion from the Ethics Committee (Comité de Protection des Personnes, CPP) in accordance with Article L1121-4 of the French Public Health Code.

### Protocol Amendments

Only the sponsor is authorized to modify the protocol, in consultation with the coordinating investigator.

A substantial amendment refers to any modification that significantly impacts any aspect of the research, including the protection and safety of participants, the validity of the study, the quality and safety of the investigational product, the interpretation of scientific documentation supporting the study, or the study’s conduct.
A request for approval of a substantial amendment will be submitted by the sponsor to the ANSM, the CPP, or both, depending on the nature of the change, for authorization and/or opinion. Once authorization and/or a favorable opinion has been received, the amended version of the protocol will be distributed by the sponsor to all investigators.

A non-substantial amendment refers to a minor change or clarification with no impact on the conduct of the trial. Such modifications will not be submitted to the authorities but will be agreed upon between the sponsor and the investigator and clearly documented in the study’s follow-up file.

### Participant Information and Consent

In accordance with current regulations, participants must receive complete and understandable information through a Participant Information Sheet specifically prepared for the study and approved by the Ethics Committee. This information will be provided and explained by the investigator.
The investigator must ensure that participants are fully informed about potential risks and constraints associated with participation in the study.

Participants will be given sufficient time to ask questions and to make an informed decision.
They must then sign the Informed Consent Form in the presence of the investigator who presented the study, and the document must be dated on the day of signing. One copy will be given to the participant, one retained by the investigator, and one filed in the participant’s medical record.

The investigator must ensure compliance with all inclusion and exclusion criteria prior to enrollment. No study-specific procedures may take place before the participant has been fully informed and has provided written consent.
Participants may withdraw their consent at any time, and any new information relevant to their safety will be promptly communicated to them.

### Data Protection and CNIL Compliance

In accordance with the Reference Methodology MR-001, data processing will be carried out under the confidentiality conditions defined by the amended French Data Protection Act of January 6, 1978, and in compliance with the European General Data Protection Regulation (GDPR).

The data controller is Lille University Hospital (CHU de Lille), acting as the sponsor, whose contact details are:
Direction de la Recherche et de l’Innovation – Maison Régionale de la Recherche Clinique, Hospitalière et Universitaire,
[name].

In accordance with the GDPR, data from this study will be processed for the purpose of scientific research (Article 6) within the framework of a mission of public interest (Article 9) for which the sponsor is responsible.
The data will be stored on the secure CHU Lille network and will be pseudonymized.

In compliance with Article L1121-1-1 of the French Public Health Code and Articles 17.3.c and 17.3.d of the GDPR, participants have the right to request the erasure of their data and to object to its processing. They will be informed that data collected prior to withdrawal of consent may not be deleted and may continue to be processed under the conditions defined for the research.
Participants also have the right to request restriction of processing in accordance with Article 18 of the GDPR, and to lodge a complaint with the supervisory authority (CNIL in France).
In accordance with Article 13 of the GDPR, when personal data are collected directly from the participant, the data controller must provide all relevant information required by this article at the time of collection.

For the purpose of the research, personal data will be processed to allow analysis of study results in relation to the study objectives.
To this end, medical and other data concerning participants may be transmitted to the sponsor or to third parties or organizations acting on behalf of the sponsor, in France or abroad, including outside the European Union, provided that the destination country ensures an adequate level of data protection as recognized by French authorities.
These data will be identified by a unique code number and participant initials.
Under conditions ensuring confidentiality, data may also be transmitted to French and foreign health authorities.

All study-related data will be archived for a minimum of fifteen years from the end or early termination of the study, in accordance with applicable legislative and regulatory provisions.

## 15 FUNDING AND INSURANCE

### Funding

The study is funded by the **Horizon-ERC-POC grant (ERC-2022-POC2 to [name], grant agreement n° 101111874/GRASP)**

***Insurance***

The sponsor will obtain an insurance policy covering its civil liability as well as that of all study personnel, in accordance with Article L1121-10 of the French Public Health Code.
The study may not begin until this insurance coverage has been secured.

### PUBLICATION AND DISSEMINATION OF RESULTS

#### Decision on Publication

The final study report will be written by the coordinating investigator, [name], in collaboration with her research team.

In accordance with Article R5121-13 of the French Public Health Code, no written or oral communication about this trial may be made without the joint agreement of both the investigator and the sponsor.
All publications must state that Lille University Hospital (CHU de Lille) is the sponsor of the study.
In any case, CHU de Lille, as the sponsor, retains control over the first publication.
The investigator will provide the sponsor with a copy of any intended publication or presentation.

#### Publication Rules

[name] and [name] will be included as first or last authors on all resulting publications.
The sponsor retains exclusive ownership of all study results and related data.
These results and all research data may not be transmitted to any third party without prior negotiation and formal agreement with the Directorate for Research and Innovation.
Any such request must be communicated as early as possible to the Legal Affairs Office of the Directorate for Research and Innovation.

#### Publication of Ancillary Studies

Not applicable.

| 68-70 | 5 280-5 600 | 132-140 | 264-280 | 7.0 | 9.0-10.0 |
| 71-75 | 5 680-6 000 | 142-150 | 284-300 | 7.0 | 9.0-10.0 |
| 76-80 | 6 080-6 400 | 152-160 | 304-360 | 7.0 | 9.0-10.0 |
| 81-85 | 6 480-6 800 | 162-170 | 324-340 | 7.0 | 9.0-10.0 |
| 86-90 | 6 880-7 200 | 172-180 | 344-360 | 7.0 | 9.0-10.0 |
| 91-95 | 7 280-7 600 | 182-190 | 364-380 | 7.0 | 9.0-10.0 |
| > 96 | 7 680-8 000 | 192-200 | 384-400 | 7.0 | 9.0-10.0 |
|  | | | | | |

Annexe 3 : Biological Sample Flow and Management

| **Parameters to be Analyzed** | **Matrix** | **Baseline Sampling (T0)** | **Intermediate Time Points (every 10 min for 8 h)** | **Final Time Point (T0 + 8 h)** | **Use (Clinical Care or Research)** | **Transport Conditions / Delivery Time (if applicable)** | **Frequency of Shipment or Receipt** | **Location and Responsible Laboratory** | **Final Disposition of Samples** |
| --- | --- | --- | --- | --- | --- | --- | --- | --- | --- |
| LH | Blood | – | 1 dry tube (1.5 mL) | – | Research | Immediate transport (room temperature) | As participants are enrolled | CBP Biochemistry Laboratory | Destruction after analysis |
| LH, FSH, E2, Total Testosterone | Blood | 1 dry tube (5 mL) | – | 1 dry tube (5 mL) | Research | Immediate transport (room temperature) | As participants are enrolled | CBP Biochemistry Laboratory | Destruction after analysis |
| AMH | Blood | 1 dry tube (5 mL) | – | 1 dry tube (5 mL) | Research | Immediate transport (room temperature) | As participants are enrolled | CBP Biochemistry Laboratory | Destruction after analysis |
| Androstenedione | Blood | 1 dry tube (5 mL) | – | 1 dry tube (5 mL) | Research | Immediate transport (room temperature) | As participants are enrolled | CBP Biochemistry Laboratory | Destruction after analysis |
| **TOTAL** | Blood | 3 dry tubes (5 mL) | 49 dry tubes (1.5 mL) | 3 dry tubes (5 mL) | Research | Immediate transport (room temperature) | As participants are enrolled | CBP Biochemistry Laboratory | Destruction after analysis |

**Notes:**

- TAL: immediate transport to the analysis laboratory.
- All samples are collected exclusively for research purposes.
- Samples will be destroyed after completion of analyses, with no biological collection or biobank constituted.

### Annex 4: Summary of Product Characteristics (SmPC) for Ganirelix*

**Source:** Vidal Database
**Section:** Medicinal Products
**Last Update:** July 29, 2021

**ORGALUTRAN^®^
ganirélix**

[Formes et présentations](http://hoptimal.chrul.net/showProduct.html?productId=18619#forme)|[Composition](http://hoptimal.chrul.net/showProduct.html?productId=18619#compo)|[Indications](http://hoptimal.chrul.net/showProduct.html?productId=18619#indic)|[Posologie et mode d'administration](http://hoptimal.chrul.net/showProduct.html?productId=18619#posol)|[Contre-indications](http://hoptimal.chrul.net/showProduct.html?productId=18619#contr)|[Mises en garde et précautions d'emploi](http://hoptimal.chrul.net/showProduct.html?productId=18619#mises)|[Interactions](http://hoptimal.chrul.net/showProduct.html?productId=18619#inter)|[Fertilité/grossesse/allaitement](http://hoptimal.chrul.net/showProduct.html?productId=18619#gross)|[Conduite et utilisation de machines](http://hoptimal.chrul.net/showProduct.html?productId=18619#machi)|[Effets indésirables](http://hoptimal.chrul.net/showProduct.html?productId=18619#effet)|[Surdosage](http://hoptimal.chrul.net/showProduct.html?productId=18619#surdo)|[Pharmacodynamie](http://hoptimal.chrul.net/showProduct.html?productId=18619#phard)|[Pharmacocinétique](http://hoptimal.chrul.net/showProduct.html?productId=18619#pharc)|[Sécurité préclinique](http://hoptimal.chrul.net/showProduct.html?productId=18619#secur)|[Incompatibilités](http://hoptimal.chrul.net/showProduct.html?productId=18619#incom)|[Modalités de conservation](http://hoptimal.chrul.net/showProduct.html?productId=18619#condi)|[Modalités manipulation/élimination](http://hoptimal.chrul.net/showProduct.html?productId=18619#modal)|[Prescription/délivrance/prise en charge](http://hoptimal.chrul.net/showProduct.html?productId=18619#rensadm)

#### Pharmaceutical Form and Presentation

Subcutaneous injectable solution, 0.25 mg/0.5 mL (aqueous, sterile, ready-to-use, clear and colorless):
Single-use prefilled syringe of 0.5 mL with a needle fitted with a natural dry rubber/latex cap (in contact with the needle; see Warnings and Precautions), available in boxes of 1 and 5 syringes.

#### Composition

**Per syringe:**

- Ganirelix* (INN) ............................................. 0.25 mg
- Excipients: acetic acid, mannitol, water for injections.
  The pH may be adjusted with sodium hydroxide and acetic acid.

**Excipient with known effect:** This medicine contains less than 1 mmol sodium (23 mg) per injection, i.e., it is essentially “sodium-free.”

Ganirelix is a synthetic decapeptide with high antagonistic activity toward natural gonadotropin-releasing hormone (GnRH). Amino acids in positions 1, 2, 3, 6, 8, and 10 of the natural GnRH decapeptide are substituted, yielding [N-Ac-D-Nal(2)1, D-pClPhe2, D-Pal(3)3, D-hArg(Et2)6, L-hArg(Et2)8, D-Ala10]-GnRH, molecular weight 1570.4.

#### Therapeutic Indications

Orgalutran is indicated for the prevention of premature luteinizing hormone (LH) surges in women undergoing controlled ovarian hyperstimulation (COH) in assisted reproductive technology (ART) procedures.
In clinical studies, Orgalutran was used in combination with recombinant follicle-stimulating hormone (FSH) or corifollitropin alfa, a long-acting follicular stimulant.

#### Dosage and Administration

Orgalutran should be prescribed only by specialists experienced in fertility treatment.

**Dosage:**
Orgalutran (0.25 mg) is administered subcutaneously once daily to prevent premature LH surges in women undergoing COH. Stimulation with FSH or corifollitropin alfa begins on day 2 or 3 of the menstrual cycle. Orgalutran treatment begins on day 5 or 6 of stimulation, depending on ovarian response (number and size of growing follicles and/or circulating estradiol levels).

Daily Orgalutran injections continue until sufficient follicular development is achieved. Follicular maturation is then induced by human chorionic gonadotropin (hCG).

Due to its half-life, the interval between two injections or between the last injection and hCG administration must not exceed 30 hours to prevent a premature LH surge.

**Route of administration:**
Subcutaneous injection, preferably in the thigh. Injection sites should vary to avoid lipodystrophy. Patients may self-administer after adequate training.

#### Contraindications

- Hypersensitivity to ganirelix, GnRH, any GnRH analogs, or any excipients listed above.
- Moderate to severe hepatic or renal impairment.
- Pregnancy or breastfeeding.

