| **STUDY POPULATION** | ****Inclusion Criteria****  - Women aged **18 to 35 years** - Diagnosis of **PCOS** with **AMH > 28 pmol/L**, **LH > 8 IU/mL**, and **serum testosterone > 0.39 ng/mL** - **No hormonal treatment or contraception** for at least **2 months** prior to inclusion - **No treatment with Metformin** or any other medication affecting metabolism - **Affiliated with the French Social Security system** - **Body Mass Index (BMI)** below 30 **kg/m²**  ****Exclusion Criteria****  - **Pregnant women** - **Inability to understand the information leaflet** - **Known hypersensitivity** to Ganirelix, to any structural analog of gonadotropin-releasing hormone (GnRH), to exogenous peptide hormones, or to any of the excipients |
| **SAMPLE SIZE** | 20 women |

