| **Intervention description** | An intra-venous cannula will be inserted and blood will be sampled at 10-min intervals for a 4-h baseline period commencing at 0800 h. Ganirelix will be then administered subcutaneously at single-dose regimen at 0.0625 mg (n = 10 women with PCOS). After Ganirelix administration sampling will continue at 10-min intervals for 4 h. |
| **Name of arm 2** | Pilot phase-0, parallel, clinical study.  Test the efficacy of Ganirelix administered subcutaneously at single-dose regimen of 0.025 mg in 10 women with PCOS, in rectifying LH pulse frequency and LH amplitude. |
| **Intervention (at least one intervention)** | Drug (including placebo)  Radiation  Other  Device (including sham) Behavioral  Biological / vaccine  Genetic  Procedure / surgery  Dietary supplement |
| **Intervention name** | Ganirelix (Orgalutran) |
| **Intervention description** | An intra-venous cannula will be inserted and blood will be sampled at 10-min intervals for a 4-h baseline period commencing at 0800 h. Ganirelix will be then administered subcutaneously at single-dose regimen at 0.025 mg (n = 10 women with PCOS). After Ganirelix administration sampling will continue at 10-min intervals for 4 h. |
|  | **Primary Outcome measure** |
| **Title** | Serum LH level every 10 minutes for 8 hours |
| **Time point at which primary outcome measure is assessed** | The degree of gonadotropin suppression will be determined by calculating the percent inhibition from the pre-antagonist period [(mean PRE - nadir)/mean PRE] x 100, where nadir hormone levels will be calculated using a moving average. |
|  | **Secondary outcome measures, repeating as many times as 2nd outcomes** *Noter les 5 principaux critères d’évaluation* |
| **Title** | Measurement of serum testosterone and androstenedione, FSH, estradiol and AMH levels |
| **Time point(s) at which Secondary outcome measure is assessed** | Serum testosterone and androstenedione, FSH, AMH and estradiol levels at the beginning and at the end of the 8 hours |
| **Inclusion criteria** | -women aged 18 to 35  -women with PCOS with AMH> 28 pmol / L, LH> 8 IU / mL and testosteronemia > 0.39 ng/mL  - no hormonal treatment or contraception for 2 months  - women covered by the Social Security system  Non obese women |
| **Exclusion criteria** | -hormonal treatment or hormonal contraception  - Metformin treatment  -pregnant woman  -inability to understand the newsletter |

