### ****6.2 Exclusion Criteria****

- Ongoing treatment with **medications affecting metabolism**, such as **metformin**
- **Pregnant woman**
- **Inability to understand** the information sheet
- **Hypersensitivity** to the active substance Ganirelix, to any **structural analogues of gonadotropin-releasing hormone (GnRH)**, to **exogenous peptide hormones**, or to any **excipients**
- **Administrative reasons**, including:
  - Inability to receive adequate informed information
  - Inability to participate in the entire study
  - Lack of **social security coverage**
  - **Refusal to sign** the informed consent form

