# INVESTIGATIONAL MEDICAL PRODUCT

### ****8.1 Name and Description of the Investigational Medicinal Product (IMP)****

**Orgalutran® 0.25 mg** (Ganirelix) will be used at doses **significantly lower** than the recommended therapeutic doses.

For this pilot study:

- **10 participants** will receive an injection corresponding to **one-quarter of the standard dose** (Experimental Group 1), and
- **10 participants** will receive an injection corresponding to **one-tenth of the standard dose** (Experimental Group 2).

The **dilution**of the investigational product will be performed by the **qualified study nurse** prior to administration.

See the **Summary of Product Characteristics (SmPC)** for Ganirelix (Annex 4).

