#### Fertility, Pregnancy, and Lactation

- **Pregnancy:** Contraindicated.
- **Lactation:** Contraindicated. Unknown if excreted in breast milk.
- **Fertility:** Used to prevent premature LH surges during COH for ART procedures.

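### Breastfeeding and moderate or worse liver or kidney impairment, both contraindicated in the annexed product label, are missing from every exclusion list

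*Protocol*

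**What the plan says.** Annex 4, under Contraindications, has three entries. The first is hypersensitivity to the product, to GnRH or its analogues, or to the excipients. The second is "Moderate to severe hepatic or renal impairment". The third is "Pregnancy or breastfeeding". Under Fertility, Pregnancy, and Lactation the annex returns to breastfeeding: "Contraindicated. Unknown if excreted in breast milk".

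The protocol states its exclusions in three places:

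- **Section 6.2** lists medication affecting metabolism, "Pregnant woman", inability to understand the information sheet, hypersensitivity, and administrative reasons.
- **The full synopsis** lists "Pregnant women", inability to understand the leaflet, and hypersensitivity.
- **The registration synopsis** lists hormonal treatment or contraception, metformin, "pregnant woman", and inability to understand the written information.

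Section 8.1 refers the reader to the product characteristics in Annex 4. Section 14, Participant Information and Consent, sets the check before enrolment: "The investigator must ensure compliance with all inclusion and exclusion criteria prior to enrollment".

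**The concern.** Section 6.2 carries over only part of what the annexed label forbids. It takes the hypersensitivity entry and half of the pregnancy and breastfeeding entry, then drops the other half and the whole entry on liver and kidney impairment. No reason is given, so this reads as an incomplete transfer rather than a decision to dose against the label.

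What is at stake is participant safety. A woman who is breastfeeding, or who has significant liver or kidney disease, could satisfy every written criterion and receive the injection. The synopsis says that no individual benefit is guaranteed, so there is little to set against a labelled contraindication. Keeping her out would depend on the investigator's knowledge of the drug or on someone consulting the annex. Endpoints and analyses are not touched.

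**Working it through.** There is no figure in the plan to reproduce; the check is a comparison of texts.

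**Step 1. Each Annex 4 contraindication against each exclusion list.**

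| Contraindication in Annex 4 | Section 6.2 | Full synopsis | Registration synopsis | Lists covering it |
| --- | --- | --- | --- | --- |
| Hypersensitivity | yes | yes | no | 2 of 3 |
| Liver or kidney impairment, moderate or worse | no | no | no | 0 of 3 |
| Pregnancy | yes | yes | yes | 3 of 3 |
| Breastfeeding | no | no | no | 0 of 3 |

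Of the annex's three entries, section 6.2 therefore carries one in full, one in half and one not at all. The operative omission is the one in section 6.2; the synopses repeat it.

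**Step 2. Could another clause close the gap?**

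- The inclusion criteria (section 6.1 and both synopses) cover age, BMI, hormone thresholds, recent hormonal treatment, insurance and similar matters, with a minimum weight in section 6.1. None concerns lactation or organ function.
- Section 8.1 points to the product characteristics but does not make their contraindications exclusions.
- The check in section 14 is against the written criteria, so a woman with either condition passes it.
- Section 13, Monitoring of the study, lists compliance with the inclusion criteria among its minimum checks, so monitoring need not catch her either.
- The withdrawal criteria in section 6.3 mention neither condition.
- The laboratory tables (Biological Analyses and Annex 3) schedule hormones only. Liver function appears only in section 5.1, as a before-and-after outcome and not as a screening test.

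Nothing in the document closes the gap.

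**Step 3. Size of the exposure.** The labelled dose is 0.25 mg once daily (Annex 4, Dosage). Each participant receives one injection (section 7.2):

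- lower dose: 0.025 / 0.25 = 0.10, or 10% of one labelled dose
- higher dose: 0.0625 / 0.25 = 0.25, or 25% of one labelled dose

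Annex 4, Overdose, reports no systemic toxicity up to 12 mg. The higher study dose lies below that by a factor of 12 / 0.0625 = 192. This is reassuring about direct toxicity. It does not bear on transfer into milk, which the annex calls unknown, or on impaired elimination. The annex gives a half-life of about 13 hours, with 75% eliminated in faeces and 22% in urine.

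**The case against.** The strongest reply is that the gap is formal and the risk remote. Each woman gets one small dose from a team that uses ganirelix routinely (section 7.1), and Annex 4 restricts prescribing to specialists. The contraindications sit inside the protocol as an annex, section 8.1 points to them, and section 14 requires conduct under good clinical practice and applicable regulation. A contraindication binds the prescriber whether or not section 6.2 repeats it, and section 14 does not say that the eligibility check is the only medical check before dosing.

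This stands as a limit on likelihood and consequence. It does not remove the written gap: a protocol that excludes pregnancy and hypersensitivity by name should not leave the remaining contraindications to be inferred.

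A second reply is that the change may cost more than two lines of text. Section 14, Protocol Amendments, treats a change that significantly affects participant protection and safety as substantial, to be submitted to the competent authority, the ethics committee or both. That is fair. The classification is the sponsor's, but the possible submission belongs in the cost.

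Severe allergic conditions are a separate and weaker matter. The synopsis and section 10.2 advise against treatment there and ask for caution, but Annex 4 does not list such conditions as a contraindication. Leaving them to clinical judgement is defensible.

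**Conclusion.** The point holds. Breastfeeding and moderate or worse liver or kidney impairment are contraindicated in the annexed label and appear in 0 of 3 exclusion lists. The protocol as written would admit such women. This is a participant-safety inconsistency that should be corrected; it does not undermine the trial and has no effect on endpoints or analysis.

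The practical risk is low. Exposure is a single dose at 10% or 25% of the labelled one, and I assume that few if any of 20 women aged 18 to 35 would be affected. The protocol gives no figure for either condition, so that assumption cannot be tested from the document. The finding itself does not rest on it.

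**What to change.** Add two exclusions to section 6.2 and to both synopsis lists: breastfeeding; and known liver or kidney impairment of moderate or greater severity. State that both are checked by history and medical record, since no screening laboratory test is scheduled that would show the second. Add the matching items to the eligibility checklist.

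As a lesser consistency point, severe allergic conditions could be listed too, to match the synopsis and section 10.2. The main correction does not depend on it.

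The cost is two lines of eligibility wording (three with allergy) and the checklist items, with no new laboratory test. If the criteria are already approved and the sponsor classes the change as substantial, a submission is needed as well. The downside is the possible loss of a few otherwise eligible candidates.
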